#### Study IV: consequences of steroid treatment for BMD, body composition, and also vasculitis/vascular stiffness in polymyalgia rheumatica and giant cell arteritis patients: 1-year prospective study

3.4.4

Patients who are diagnosed with PMR/GCA are at high risk of osteoporosis due to both disease inflammatory process and corticosteroid treatment. Nonspecific bone protection (lifestyle intervention) should be initiated at the time of steroid therapy, and specific antiosteoporotic therapy soon thereafter in patients with low BMD. The gold standard for the diagnosis of osteoporosis is regional dual energy X-ray absorptiometry (DXA) of the hip and spine. Whole-body DXA can estimate 3 body compartments consisting of fat mass (FM), lean body mass (LBM), and bone mass. DXA is currently considered the gold standard for body composition assessment. Changes in whole body bone mineral content (BMC) is a biological meaningful measure of overall calcium balance over a time period, whereas changes in regional BMD are probably more predictive for fracture risk. Changes in body composition due to inflammatory process have previously been reported in rheumatoid arthritis.^[41–43]^ Patients with PMR/GCA are also exposed to different changes in body compositions mainly due to inflammatory process; however, this has not been evaluated before.

The vasculitis process in patients with classic cranial GCA preferentially involves the extracranial branches of the carotid artery; however, large vessel involvement of the aorta and its primary and secondary branches may be involved in patients with LV-GCA.^[4]^ The extent of large artery involvement of GCA is uncertain, but clinically apparent large-vessel disease comprises an estimated 9% to 14% of cases. ^[44,45]^ LV-GCA patients have symptoms and signs of vascular insufficiency and are usually diagnosed with delays due to atypical manifestations, and also inadequacy of GCA criteria for classifying these patients.^[4]^

Arterial distensibility has been defined as a measure of the artery's ability to expand and contract with cardiac pulsation and relaxation. Vasculitis and other risk factors (eg, aging, hypertension, and arteriosclerosis) may cause alteration in the structural and functional properties of the arterial wall, which results in diminished arterial distensibility. When evaluating arterial stiffness, the aorta is a main vessel of interest, because of substantial contribution of abdominal and thoracic aorta to the arterial buffering function.^[46,47]^ Pulse wave velocity (PWV) measurement is a simple, noninvasive, and reproducible method to evaluate aortic stiffness, and can be measured from different arterial sites. Common carotid artery and the femoral artery are 2 common sites to obtain pressure waveforms transcutaneously. The distance covered by the waves is corrected to the surface distance between the 2 recording sites and base of aorta (eg, jugulum), and the time delay (or transit time) is measured using the feet of the 2 waveforms (at the end of diastole, when the steep rise of the wave front begins). PWV is subsequently measured as the ratio of the distance to the time delay (PWV [m/s] = distance [m]/transit time [seconds]).^[46]^ Previous study was in favor of that PMR is associated with increased aortic stiffness which may improve upon reduction of systemic inflammation induced by treatment with glucocorticoids.^[48]^

This study is a 1-year prospective investigation which assesses 2 different areas of concern in PMR/GCA patients, namely BMD plus body composition and vasculitis/vascular stiffness of large vessels (aorta). The following procedures will be performed in all included patients:1.PWV measurement of aorta at baseline and then every 3 months to assess large vessels involvement (aorta). The results of PWV assessment, which will be automatically calculated from measurements of pulse transit time and distance between the 2 sites, will be compared with vasculitis found in the 18F-FDG PET/CT (study I). The results of PWV of aorta will also be assessed regarding the actual cumulated prednisolone dose to find out the effects of steroid treatment on the arterial stiffness.2.Whole-body DXA scan at baseline and after 1 year from the initiation of study to evaluate BMD and body compositions. The degree of the difference in the T score and body composition (including lean body mass, fat mass, bone mineral content, and BMD) will be compared with the cumulated prednisolone dose and the total global disease burden of the 18F-FDG PET/CT scan at baseline (study I).

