### Statistical analysis

3.12

It is anticipated that 80 participants are likely to be included during a period of 1 year. The results will be considered as significant if *P* value <0.05. Statistical analysis has been discussed below with respect to each individual study.

In study I, data will be descriptive (mean ± standard deviation). Comparisons of the data, between the PET-positive and PET-negative patients, will be made with the Mann–Whitney *U* test or Student *t* test, depending on whether or not the distribution is normal. When comparing 2 binary variables, the chi-square test will be performed. Correlation analysis will be performed with Pearson correlation test.

Study II consists of descriptive statistics and proportions of agreement.

Study III consists of descriptive statistics. Comparisons between groups will be made with McNemar test. The sample size of 80 patients is sufficient to indicate a difference of 15% in detection rate of malignancies with 18F-FDG PET-CT scan as opposed to CXR plus abdominal UL (with a significance level of 5% (1-sided), power of 80%, and assuming discordant proportions of 15% and 0%).^[52]^

Study IV consists of descriptive statistics. Univariate comparisons between groups will be made with the Mann–Whitney *U* test or Student *t* test, depending on whether or not the distribution is normal. When comparing 2 binary variables, the chi-square test will be performed. Analysis of repeated measurements over time will be done by means of mixed linear models, using standard errors that allow for intragroup correlation, relaxing the usual requirement that the observations be independent. Comparison of the above mentioned baseline data, matched by age and sex, will be made, to the extent that these data are available.

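### Study IV sets aortic PWV against PET vasculitis in non-randomised groups, and the only between-group tests named for it are unadjusted, so a difference by PET status may be spurious or masked

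*Protocol article*

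**What the plan says.** Section 3.4.4 (Study IV) of the protocol article plans "PWV measurement of aorta at baseline and then every 3 months to assess large vessels involvement (aorta"). It says the PWV results "will be compared with vasculitis found in the 18F-FDG PET/CT (study I"). It attaches no test, time point or covariate to that comparison.

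The same section gives the background on stiffness: "Vasculitis and other risk factors (eg, aging, hypertension, and arteriosclerosis) may cause alteration in the structural and functional properties of the arterial wall". It also cites earlier work linking polymyalgia rheumatica (PMR) to "increased aortic stiffness which may improve upon reduction of systemic inflammation induced by treatment with glucocorticoids".

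The Study IV paragraph of section 3.12 (Statistical analysis) contains three relevant statements:

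- "Univariate comparisons between groups will be made with the Mann–Whitney *U* test or Student *t* test", the choice depending on normality. A chi-square test covers pairs of binary variables.
- "Analysis of repeated measurements over time will be done by means of mixed linear models, using standard errors that allow for intragroup correlation". No fixed effects are listed.
- "Comparison of the above mentioned baseline data, matched by age and sex, will be made, to the extent that these data are available". The comparator is not identified.

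Section 3.4.4.2 has blood pressure measured before PWV. Section 3.12 gives it no role in the analysis.

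**The concern.** PWV is measured to show whether the aorta is involved, and setting it against PET vasculitis asks whether it does so. That is a question of attribution between groups formed by a scan result. Nothing in the design makes those groups alike in age or blood pressure, and section 3.3 sets a lower age limit but no upper one. An unadjusted two-group test cannot separate vasculitis from the other causes of stiffness that the protocol names.

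If PET-positive patients happen to be older or more hypertensive, a difference may be credited to vasculitis when there is none. If they happen to be younger or less hypertensive, a real difference may be hidden. In both cases the stated test does not support a conclusion about PWV as a marker of large-vessel involvement.

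**Working it through.** The protocol gives no sample size, standard deviation or effect size for the PWV–PET comparison, so there is no figure of its own to reproduce. The check has two parts.

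**1. What the text provides against confounding**

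| Provision in section 3.12 | Deals with age? | Deals with blood pressure? | Tied to PET status? |
|---|---|---|---|
| Univariate t / Mann–Whitney tests | No | No | By inference: the only between-group tests named for a continuous Study IV outcome |
| Mixed linear models over time | Not stated | Not stated | Not stated |
| Age- and sex-matched baseline comparison | Yes, if data are available | No | Unclear: could be PET groups or an outside reference |

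Secondary outcome 6 (section 3.8) describes PWV over time in the included patients, not by PET group. No row clearly adjusts the PWV–PET contrast.

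**2. How large the distortion could be**

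From the protocol: N = 80 and alpha = 0.05. Two-sided testing is assumed, because sidedness is not stated for Study IV.

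Assumed, not from the protocol: correlation r of PWV with age 0.5 (range 0.3 to 0.6); age gap between PET groups 0.5 SD (range 0.25 to 0.75); no true vasculitis effect; the PET split.

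Spurious difference in PWV SD units = r × age gap:

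- central: 0.5 × 0.5 = 0.25
- low: 0.3 × 0.25 = 0.075
- high: 0.6 × 0.75 = 0.45

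Rejection probability comes from the noncentral t with 78 df and ncp = difference / √(1/n₁ + 1/n₂). For 25/55, √(1/25 + 1/55) = 0.241, so the central ncp is 0.25/0.241 = 1.04. For 10/70, √(1/10 + 1/70) = 0.338, so ncp = 0.25/0.338 = 0.74.

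| Split PET+/PET− | 0.075 SD | 0.25 SD | 0.45 SD |
|---|---|---|---|
| 40/40 | 6.3% | 19.7% | 51.1% |
| 25/55 | 6.1% | 17.6% | 45.3% |
| 20/60 | 6.0% | 16.0% | 40.6% |
| 10/70 | 5.6% | 11.3% | 26.0% |

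The nominal rate is 5%. With no age gap the test keeps it.

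**Simulation with different assumed inputs** (4,000 replicates): PWV slope 0.1 m/s per year, age SD 8 years, between-patient residual SD 1.8 m/s, within-patient SD 0.8 m/s. Bias = slope × gap = 0.1 × 5 = 0.50 m/s for a 5-year gap.

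| PET+ older by 5 years, no true effect | 40/40 | 20/60 |
|---|---|---|
| Unadjusted baseline t test | 17.1% | 14.5% |
| Baseline model adjusted for age | 5.6% | 4.8% |
| Between-group difference in change from baseline | 4.8% | 4.9% |

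With the sign reversed (PET-positive 5 years younger, true difference 1.0 m/s, 40/40), the apparent difference is 1.0 − 0.5 = 0.50 m/s. Power is 18% unadjusted and 56% adjusted for age.

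**The case against.** Section 3.4.4 does not attach the univariate test to the PWV–PET comparison, and does not limit that comparison to baseline. Both are readings of the text. The article is condensed, and model terms are often left to an analysis plan that is not shown. The secondary objectives are described as hypothesis generating (section 3.9), the planned PWV paper concerns steroid effects (section 3.18), and adjustment would still be possible at analysis because the data are collected. This lowers the stakes, and the link to the test should be labelled an inference. It does not remove the point: the word univariate is a stated choice, not a silence, and it is the only route section 3.12 offers for a continuous between-group comparison in Study IV.

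A reader might infer more than the text supports, in four ways:

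- **That the repeated PWV data go unused.** Mixed models for repeated measurements are planned. What is missing is any tie to PET status or to covariates.
- **That age is ignored altogether.** The matched baseline comparison is a partial provision, though conditional, of unclear comparator and without blood pressure.
- **That PET-positive patients will look stiffer because they are older.** Nothing in the protocol says they are older, so the direction of bias is unknown.
- **That a PET-by-visit term would be the main proof of reversible vasculitis.** It cancels stable age effects, but it still mixes resolution of vasculitis with blood-pressure change and with steroid exposure, which may differ by PET group, since the Introduction says GCA needs higher doses than PMR. Section 3.4.4 also links treatment-responsive stiffness to systemic inflammation in PMR generally, so PET-negative patients could improve too.

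**Conclusion.** The point holds as a moderate one that should be addressed. As section 3.12 stands, the named between-group method gives a PWV–PET contrast confounded by factors the protocol itself lists, and neither the matched comparison nor the mixed models clearly repairs it. The distortion could run either way. Its size rests entirely on assumed inputs: about 18% false positives at a nominal 5% with a 25/55 split (6% to 45% over the assumed ranges) and about 11% with 10/70 (6% to 26%). These figures show what modest imbalance can do; they do not predict what this cohort will show.

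**What to change.** In section 3.12, for the PWV–PET question:

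1. Replace the univariate test with a linear model of baseline aortic PWV on PET vasculitis, adjusted for age, sex and blood pressure at the PWV visit. Report the estimate with its 95% CI.
2. Because blood pressure may partly be a consequence of stiffness, also report the model with age and sex only.
3. As a supportive analysis, add PET status and PET × visit to the planned mixed model for the five PWV visits (baseline and weeks 12, 24, 36 and 48), with age, sex and blood pressure at each visit. State that steroid exposure may differ by PET group, so this term alone does not isolate resolution of vasculitis.
4. State who is compared with whom in the age- and sex-matched baseline comparison.

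The cost is a few lines of text and a few degrees of freedom out of 80 patients. Baseline age and sex and the repeated PWV values are part of the planned data, and section 3.4.4.2 already places a blood pressure reading before PWV. No extra visit or measurement is needed.

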##### Body composition measurement

3.4.4.1

Body mass index (BMI) of patients will be calculated from weight/height^2^. Individuals with BMI values <18.5 kg/m^2^ are considered underweight, 18.5 ≤ BMI < 25 as normal, 25≤ to <30 as overweight. BMI values ≥30 indicates obesity.^[49]^ LBM, FM, BMD, BMC, and fat-free mass (FFM = LBM + BMC). FM and FFM will be expressed as absolute kg and FM as percentage of total mass as well. The reference value for FM% is 12% to 20% for men and 20% to 30% for women.^[50]^ FFM and fat mass indices (FFMI and FMI) will also be calculated. An aged and sexed matched European reference from Switzerland will be used for cut-off values for being under lean and obese.^[51]^

Bone mineral density values will be presented as Z scores (the number of standard deviations from the mean in healthy age and sex-matched people) and T scores (the number of standard deviations from the mean in healthy young sex-matched people). T score ≤−2.5 will be considered as osteoporosis and T score <−1 as osteopenia.

##### PWV assessment

3.4.4.2

After measuring blood pressure (BP), aortic (aorta to femoral) and upper limb (aorta to radial) PWV will be measured using SphygmoCor device. Aortic PWV will be calculated from measurements of bulbus aorta and femoral artery, and upper limb PWV will be calculated from measurements of bulbus aorta and radial artery waveform. Aortic augmentation index (the difference between the second and first peaks of the central arterial waveform expressed as a percentage of the pulse pressure) with a standardization to a heart rate of 75 beats per minute will also be assessed, which is a predictor of adverse cardiovascular events.

### Clinical evaluation and laboratory tests (study I–IV)

3.5

Blood pressure, pulse, weight, and also BMI of all patients will be collected at the first visit. The following laboratory tests will be recorded: hemoglobin, white blood cells and thrombocytes, erythrocyte sedimentation rate, C-reactive protein, sodium, potassium, lipid profile, thyroid-stimulating hormone (TSH), hemoglobin A1c (HbA1C), blood sugar, creatinine, liver function test (LFT), alkaline phosphatase, calcium, vitamin D, creatine kinase, immunoglobulin A, immunoglobulin M, immunoglobulin G, antinuclear antibody (ANA), antineutrophil cytoplasmic antibody (ANCA), IgM rheumatoid factor (IgM RF), anticyclic citrullinated peptide (anti-CCP), S-fibrinogen, prostate-specific antigen (PSA), M component (blood and urine), serum-free light chains (sFLC), urine protein, urine analysis, and electrocardiogram.

### Treatment plan

3.6

#### Steroid treatment

3.6.1

Steroid treatment is based on a modification of the Danish Rheumatology Association Guidelines. Dose reduction or dose increase is also according to this guideline. Prednisolone will be initiated after performing 18F-FDG PET/CT scan (Table 2).

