## Introduction

1

Polymyalgia rheumatica (PMR) is the most common inflammatory rheumatic disease that affects individuals over the age of 50 years. The typical symptoms of PMR are bilateral aching and stiffness in selected muscle groups, predominantly in the neck, shoulders, upper arms, and pelvic girdle that are most pronounced in the morning and improve with physical activity.^[1–3]^ Giant cell arteritis (GCA) is an inflammatory vasculopathy that typically involves medium and large arteries.^[4]^ Though involvement of the extracranial branches of the carotid artery can be identified in the classic cranial GCA, GCA may also involve aorta and its major branches, predominantly branches of the proximal aorta, that is, subclavian, axillary proximal brachial arteries, representing a subset of patients with large-vessel GCA (LV-GCA).^[4,5]^ Vasculitis, if untreated, can result in ischemic complications, such as ischemic optic neuropathy, which is responsible for vision loss in 10% to 15% of patients. Whereas the etiology of PMR/GCA is still unknown, genetic and environmental factors may play roles in the development of PMR/GCA. GCA and PMR share many pathogenetic and epidemiological features, and are frequently thought to represent different spectrums of the same clinical entity. Despite the high association between PMR and GCA, it is essential to differentiate these 2 conditions due to different steroid treatment regimes. Corticosteroids are considered the treatment of choice for PMR/GCA, with higher doses required for GCA.^[1–3]^ PMR/GCA is generally not associated with reduced longevity; however, patients with aortic aneurysm/dissection have higher rates of mortality.^[6]^ Additionally, patients are at risk of different comorbidities, both due to the disease characteristic itself and also due to treatment side effects.

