With regard to vasculitis, recent literature emphasizes the ability of 18F-FDG PET/CT to assess inflammation in the vessel walls, whereas FDG uptake patterns in PMR are not yet firmly established. It may locate disease at an earlier stage than conventional imaging and assess response to therapy. Response assessment is based on changes in glucose metabolism from baseline to post-treatment follow-up, and the rates of change are different in responders and nonresponders.^[21]^ Besides locating focal disease, 18F-FDG PET/CT may also assess disease activity more globally, which may be especially interesting in systemic inflammatory diseases. Thus, this research protocol will also incorporate assessment of global disease assessment (ie, “global disease burden”), a novel approach to quantifying disease. By way of novel software-based quantitative methods, the radioactivity throughout the body can be quantified, summed, and presented as 1 single number, the systemic inflammatory activity or “global disease burden.” The method is new and not yet firmly established, but it holds significant promise, especially for response assessment in systemic inflammatory diseases.^[22,23]^

Therefore, we plan to conduct a prospective study to explore the role of 18F-FDG PET/CT scan in the management of PMR/GCA. In addition, 3 significant areas of concern in the management of PMR/GCA including: osteoporosis due to steroid treatment or disease characteristics itself, malignancy, and vasculitis/vascular stiffness will be investigated during the project. This research protocol consists of four separate studies designed to achieve below mentioned objectives that are discussed individually later in the text (Fig. 1).

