### Participants

3.3

All new patients with clinical suspicion of PMR/GCA will be offered to be included in the study. At least 5 (A–E) components of the PMR diagnostic criteria, including: age ≥50 years, bilateral shoulder or hip pain, morning stiffness lasting >45 minutes, elevated ESR, elevated CRP, disease duration >2 weeks, should be met to suspect PMR.^[3]^ For GCA, the following criteria must be considered: age >50 years, ESR/CRP >50, and also at least 2 symptoms related to vasculitis (scalp tenderness, vision disturbances, headache [new or changed], jaw claudication, tenderness of the temporal arteria) if patients do not simultaneously have PMR. If the patient is suspected for PMR, 1 cranial symptom is enough to suspect GCA. Besides, clinical suspicion of LV-GCA, that is, upper-extremity claudication, upper-extremity blood pressure discrepancies, and abnormal radial pulse, will be registered.

The exclusion criteria (study I–IV) are as follows:1.Patients with dementia or inability to communicate in Danish2.Infections or malignancy when prednisolone is permanently unsuitable3.Contraindication to imaging studies (pregnancy and blood sugar [BS] >8 mmol/L after 6 hours fasting)4.Initiation of steroid treatment before the 18F-FDG PET/CT scan5.Inability to provide informed consent

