#### Study I: the association of clinical picture of polymyalgia rheumatica and giant cell arteritis with 18F-FDG PET/CT findings: 1-year, prospective, blinded explorative study

3.4.1

The current study is a 1-year prospective, blinded, and explorative study. This is the first study of its kind, to our knowledge, to evaluate the association between the clinical picture of PMR/GCA and 18F-FDG PET/CT findings in a prospective setting. Previous study revealed the correlation between serological markers of inflammation and FDG accumulation in PMR.^[7,26–28]^ However, the small sample size was a major limitation. On the contrary, some reports failed to show this correlation.^[9,29,30]^

All included patients initially will undergo an 18F-FDG PET/CT scan. The results of the 18F-FDG PET/CT scans will not be made accessible to the treating physician in daily clinical routine, but unexpected findings or findings requiring further diagnostic tests or intervention will be relayed to the chief physicians responsible for inclusion. The results of 18F-FDG PET/CT scan will be blinded for both the clinicians and patients. During the year after the initial 18F-FDG PET/CT scan, the following clinical data will be monitored: cumulated prednisolone doses (using patient diaries), well-being of the patients (including visual analog scale [VAS], patient's assessment of pain, morning stiffness [minute], VAS for physicians’ evaluation), ESR, CRP, fibrinogen, and the eventual number of relapses. Definition of remission and relapse is based on expert opinion considering the following parameters: patient's assessment of pain, morning stiffness, ESR, CRP, clinical examination findings (eg, shoulder pain/limitation, upper extremity blood pressure discrepancies, vascular bruits and aortic regurgitation murmur), and steroid dose which is required to control symptoms.

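### The printed order puts prednisolone after PET/CT and does not direct patients with sight-threatening symptoms to be treated first and left out of the study

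*Protocol article*

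**What the plan says.** Section 3.6.1 (Steroid treatment) fixes the sequence without qualification: "Prednisolone will be initiated after performing 18F-FDG PET/CT scan (Table 2"). Section 3.3 (Participants) backs it with exclusion criterion 4, which applies to Studies I to IV: "Initiation of steroid treatment before the 18F-FDG PET/CT scan".

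The same section offers inclusion to every new patient with clinical suspicion of PMR or GCA. The symptoms counted towards GCA are "scalp tenderness, vision disturbances, headache [new or changed], jaw claudication, tenderness of the temporal arteria". Two are needed when PMR is not also suspected, but the bar drops when it is: "If the patient is suspected for PMR, 1 cranial symptom is enough to suspect GCA".

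The Introduction names the harm of untreated vasculitis as "ischemic optic neuropathy, which is responsible for vision loss in 10% to 15% of patients".

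Section 3.10 (Recruitment) gives patients 24 hours to deliberate before consent. Section 3.1 (Study setting) locates the scan in Odense, while enrolment and most other procedures are in Svendborg. Section 3.4.2 (Study II) allows temporal artery biopsy (TAB) before steroids or up to one week after they start. No such tolerance is printed for PET/CT.

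**The concern.** The article recruits on a symptom that may herald the very complication its Introduction warns of, and then places treatment behind a study scan. Criterion 4 makes it possible to treat first, at the price of eligibility. It does not say who should be treated first. A clinician who wants to follow the document and enrol the patient finds one instruction, which is to scan and then treat.

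Two things are at stake. The first is safety: a patient with visual or other ischaemic cranial symptoms could wait for a study procedure. The second is scope: if such patients are treated first, they are absent from Study II's comparison of PET with TAB. The Discussion says PET cannot evaluate the temporal artery, so this is a group in which biopsy may show what the scan cannot. Section 3.13 (Ethical consideration) nonetheless expresses the hope that patients will be spared biopsy in future. It allows that a small number may still need it, without saying which.

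**Working it through.** The plan gives no figure on this point to reproduce, and no formula applies. The check is to follow one patient through the printed text.

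1. **Entry (3.3).** A patient with suspected PMR and new visual disturbance meets the one-symptom rule for suspected GCA and is offered inclusion. None of the listed exclusions turns this patient away for urgency.
2. **Path to the scan (3.1, 3.10).** The patient is worked up at the Diagnostic Center, referred to Rheumatology, given 24 hours to deliberate, and then scanned in Odense. This assumes that the scan, as a study procedure, follows consent. No maximum time from suspicion to scan is printed.
3. **Treatment (3.6.1).** Prednisolone follows the scan. For a patient who stays eligible, the printed wait is therefore 24 hours plus a scan interval that is not given. Only the first term is known.
4. **What the scan can contribute to the first treatment decision (3.4.1, 3.4.3).** The vasculitis reading is blinded and is unveiled after one year. The scan can still matter in other ways. It is read for malignancy before blinding, "unexpected findings or findings requiring further diagnostic tests or intervention will be relayed to the chief physicians responsible for inclusion", and criterion 2 excludes "Infections or malignancy when prednisolone is permanently unsuitable".
5. **The alternative.** If the clinician treats first, criterion 4 applies and the patient is in none of Studies I to IV. For Study II this means no contribution to PET-TAB agreement.
6. **Where an exception might sit.** Section 3.6.1 refers to a modified national guideline and to Table 2, and neither is shown. Table 2's caption describes visits for included patients with persistent response, normal CRP and no symptoms. That makes it an unlikely, though not impossible, home for an urgent rule. The full protocol is not shown either.

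Neither effect can be sized from these inputs. The article gives no number of urgent presentations, no time to scan and no risk per day of delay. The 10% to 15% in the Introduction describes vision loss. It is neither a rate of urgent presentation in this cohort nor a risk attributable to a short wait.

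**The case against.** The strongest reply is that this is an argument from silence in a condensed article. Emergency handling is the kind of detail left to a full protocol or to the guideline cited in 3.6.1. Criterion 4 already presupposes that some patients are treated before the scan, and nothing forbids it. Before consent the patient is not in the study, and no sentence says treatment is withheld during deliberation. A steroid-naive scan also has a reason: the Introduction explains that "Response assessment is based on changes in glucose metabolism from baseline to post-treatment follow-up", and the Discussion frames the work as imaging before steroids.

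Much of this stands. A reader might infer that the protocol forbids urgent treatment. It does not, because criterion 4 is an eligibility exit and not a ban. A reader might also infer that the scan is useless to the treating clinician because it is blinded, but the malignancy read and the relayed findings contradict that. Nor does the sentence in 3.13 about no further risk clearly deny a treatment delay, since it follows a sentence on blood samples and may concern only those.

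On Study II, a reader might infer that the agreement is biased or that cranial GCA is missing. The text does not support either. Patients with cranial symptoms who have not been treated before the scan remain eligible, so disease that PET cannot see can still appear as discordance. Study II is also descriptive, and the secondary objectives are stated to be hypothesis-generating.

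The objection does not dispose of the sequence itself. That is not merely a missing detail: the article states an order, without qualification, for a population that includes patients with warning symptoms. An exit that nobody is told to take does not protect them.

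**Conclusion.** The point holds as a defect in the stated order of treatment and should be fixed, with moderate confidence. Followed literally, 3.6.1 can delay sight-saving treatment, and criterion 4 permits but does not direct the safe course. The conclusion rests on the printed text and would reduce to a missing cross-reference if Table 2, the guideline or the full protocol already contains an urgent rule.

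The consequence for Study II is a limit on scope and not a bias. To the extent that urgent patients are treated first, the agreement describes those whose treatment could wait for PET. That extent is unknown, and it is zero if no one is treated before the scan.

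**What to change.** In 3.6.1, state that steroids are never withheld for consent deliberation or PET/CT when visual or other ischaemic cranial symptoms are present, and that such patients are treated at once and not enrolled, under criterion 4. If Table 2 or the full protocol already says this, a cross-reference is enough.

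Two reporting steps follow. Report how many patients were excluded under criterion 4. State Study II's agreement, and any inference about avoiding biopsy, as applying to patients whose treatment could wait for PET.

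The steroid-naive design stays intact, and no visits or procedures are added. The cost is a few enrolments from the planned 80 and a narrower stated population for Study II. If the provision is new, section 3.15 requires a formal amendment sent to the ethics committee.
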